
#### Sample Size Calculation and Start of Study

Currently, there is no literature available regarding inadequate dosing of drugs in hospitalized patients with liver cirrhosis. A random sample of historical data from the clinic showed an inappropriate prescribing rate of 35%. It is expected that the recommendations will reduce this rate to 20%. To detect a significant difference between the 2 cohorts using a chi-square test with the usual .05 significance level (2 sided) and 80% power, 138 patients per group are required, resulting in a total of 276 patients.

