#### Primary and Secondary End Points

The primary end point of the study will be the comparison of the rate of deviations from the prescribed medications before and after the implementation of the consensus-validated dose recommendations. Specifically, the rate of deviations over 9 months using the recommendations (cohort B) will be compared with the rate of deviations over 9 months before their implementation (cohort A), first identified at the prescription level and subsequently aggregated at the patient level. A deviation will be defined as any prescription of a drug covered by the recommendations that does not match the corresponding recommendation for drug selection or dose adjustment, assessed at the patient level during the hospital stay. Prescriptions are assessed at the level of individual active substances. In patients with multiple relevant prescriptions, all prescriptions are checked individually for discrepancies. For the primary end point, deviations are assessed at the patient level as a binary outcome, defined as the presence of at least one deviation during the hospital stay (yes or no). Multiple deviations per patient are aggregated, with the primary outcome defined as the presence of at least one deviation per patient. The total number of MRPs per patient, including both clinically relevant (manifest or preventable) and non–clinically relevant MRPs, will be counted and subsequently dichotomized for categorical analyses. MRPs will be identified based on the first complete medication review at initial patient assessment. Combination products will be broken down into individual active substances if these are available separately; otherwise, they will be evaluated as a single entity. Physicians are given a predefined period of 3 days to address identified MRPs. Unresolved issues will be reassessed and counted thereafter. Recurring deviations after prior resolution will be counted as new events. Deviations from recommendations are treated as a process measure of prescribing behavior, whereas secondary end points are intended to characterize feasibility, acceptance, and safety-related process signals associated with implementation of the recommendations and, therefore, are interpreted as exploratory. These may include the acceptance and rejection rates of pharmacists’ recommendations, particularly for drugs with hepatotoxic properties; frequency of typical side effects (classified as “very frequent” or “frequent” according to the SmPC) of the prescribed drugs covered by the recommendations; deviations from recommended serum levels for drugs monitored via TDM; emergency readmission rates within 30 days after discharge; and overall hospital readmission rates. Furthermore, all consensus-validated recommendations rejected by the prescribing physician will be further analyzed with regard to the corresponding reasons.

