## Results

The study was supported by funding received in January 2020 (POLAR_MI) and November 2022 (INTERPOLAR-1). The clinical validation phase of this study commenced in January 2025. As of May 2026, 121 patients have been enrolled. Statistical analyses will be conducted in accordance with the predefined analysis plan. Findings from the literature review, the Delphi consensus process, and the clinical validation phase will be reported in subsequent publications. Results of the clinical validation phase are anticipated in late August 2026.

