In addition, the Child-Pugh classification [15,16] was used as the primary framework for drug selection and dose adjustment for this study. While the Child-Pugh classification reflects routine clinical practice and forms the basis of most available dosing guidance, it can only serve as a surrogate for hepatic drug metabolism and does not capture other relevant determinants of pharmacokinetics such as renal dysfunction, systemic inflammation, sarcopenia, or portosystemic shunting. Furthermore, the Delphi process is based on the simplified general model of an average hospitalized patient with cirrhosis, excluding atypical or non–cirrhosis-related comorbidities that may independently influence dosing decisions. Accordingly, the resulting recommendations should be interpreted as a basic framework requiring individualized clinical judgment in this heterogeneous patient population. A further limitation concerns the design of the clinical validation phase, which aims to analyze the feasibility and acceptability of the dose recommendations in clinical practice. The pretest-posttest, nonrandomized evaluation reflects real-world constraints but does not allow for causal inference regarding the effectiveness of the recommendations. Observed changes in prescribing behavior may be influenced by temporal effects, increased awareness, or concurrent changes in clinical practice. However, efforts will be made to mitigate these effects by maintaining a stable clinical setting across both study periods (before and after implementation of the recommendations), with consistent senior and ward physicians, and by prospectively capturing physician responses to pharmacist interventions. Both cohorts will be assessed consecutively without temporal gaps and cover comparable time frames, reducing the likelihood of structural changes in care processes or systematic differences in patient management. A prior literature review did not indicate relevant seasonal variation in disease severity of liver cirrhosis that would be expected to systematically bias the comparison. In addition, the primary end point focuses on deviations from recommendations as a process measure rather than clinical outcomes. Further clinical studies with different designs, alternative end points, and larger patient cohorts will be needed to investigate clinical outcomes on a broader scale.

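### The 276-patient target and its 80% power are not reconciled with two 9-month windows and 121 patients enrolled by May 2026

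*Protocol article*

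**What the plan says.** Cohort size is set in two ways, and progress is reported in a third place.

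- **By number.** Under Sample Size Calculation and Start of Study, "A random sample of historical data from the clinic showed an inappropriate prescribing rate of 35" per cent, and "It is expected that the recommendations will reduce this rate to 20" per cent. The comparison is planned "using a chi-square test with the usual .05 significance level (2 sided) and 80% power", from which "138 patients per group are required, resulting in a total of 276 patients".
- **By time.** Under Primary and Secondary End Points, "the rate of deviations over 9 months using the recommendations (cohort B) will be compared with the rate of deviations over 9 months" before implementation (cohort A). The Discussion adds that "Both cohorts will be assessed consecutively without temporal gaps", so the two windows cover 18 months.
- **Progress.** Under Results, "The clinical validation phase of this study commenced in January 2025" and "As of May 2026, 121 patients have been enrolled". Results of this phase are expected in late August 2026.

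The primary end point is binary per patient: at least one deviation during the hospital stay. The Statistical Analysis section tests it with a chi-square test at the .05 level and reports an odds ratio with a 95% CI.

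**The concern.** Eighteen months from January 2025 end about June 2026, which fits a results date of late August 2026. By May 2026, with about one or two months of that period left, enrolment stood at 121 of 276 (44%), leaving 155 to find. The article mentions no extension, does not say whether time or number closes a cohort, and gives no power at the size now in prospect.

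The primary comparison is a significance test. If the study closes at roughly half its planned size, a non-significant result is about as likely as a significant one even when the planned 15-point fall is real. A reader who sees 80% power in the plan would give such a result more weight than it deserves.

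A smaller point is that the 35% is called an inappropriate prescribing rate with no unit. It is not shown to be the proportion of patients with at least one deviation, which is the quantity being tested.

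**Working it through.** **Inputs from the article:** 35% and 20%; two-sided alpha .05; 80% power; 138 per group; two 9-month windows without a gap; start January 2025; 121 enrolled as of May 2026.

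**1. Reproduce the plan's figure.** Pooled-variance formula, no continuity correction, mean rate 0.275:

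n = [1.96·√(2·0.275·0.725) + 0.8416·√(0.35·0.65 + 0.20·0.80)]² / 0.15² = (1.2377 + 0.5239)² / 0.0225 = 137.9, so 138 per group. Power at 138 is 80.0%. The stated calculation is right.

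**2. Project the size at the end of the windows.** Assumptions: 121 covers both cohorts, accrual is steady and the split is equal. No days are given, so elapsed time is 16 to 17 months.

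- No further accrual: 121 in total, 60.5 per cohort.
- 17 months elapsed: 121/17 × 18 = 128 in total, 64 per cohort.
- 16 months elapsed: 121/16 × 18 = 136 in total, 68 per cohort.

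**3. Power for 35% against 20%.** Power = Φ[(0.15·√n − 1.2377)/0.6225].

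| Per cohort | Power |
|---|---|
| 60.5 | 45.5% |
| 64 | 47.6% |
| 68 | 50.0% |
| 138 (plan) | 80.0% |

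Unequal splits of 128, from 50/78 to 80/48, give 43% to 48%.

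**4. Precision and detectable effect.** The 95% CI half-width for the difference is 1.96·√[(0.2275 + 0.16)/n].

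- n = 138: 10.4 points.
- n = 64: 15.3 points, about equal to the planned 15-point effect.
- At 64 per cohort, a cohort B rate of 14% gives 79.6% power. The effect detectable with about 80% power is therefore a fall of about 21 points, not 15.

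**5. Time to reach 276.** 276/(121/16) = 36.5 months and 276/(121/17) = 38.8 months, so about 36 to 39 months against 18.

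**6. Other readings of 121.**

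- Cohort B only, begun about October 2025 and about 8 months old: 121/8 × 9 = 136. With a similar cohort A, power is about 79%.
- Cohort B only, begun January 2025, with 138 in cohort A: power is about 77%. Cohort B would then have run 16 to 17 months, which contradicts its 9-month window.

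**The case against.** **The calculation is not wrong.** This stands. The article says 138 per group are required, not that they will be reached. The fault is that target, windows and accrual are left unreconciled.

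**The lower power is a projection.** This stands too. A reader might infer that the study simply has 48% power. The documents do not support that as a fact. It assumes that 121 spans both cohorts, that accrual is steady and that the split is near equal, and the article never divides 121 by cohort. The reading in which cohort B began about October 2025 nearly meets the target. The pooled reading is still the plainer one, because in Results the count follows directly on the January 2025 start of the whole phase. The existence of both readings is itself a reason to report the split.

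**The harm is limited by what the plan already says.** This stands in part. Odds ratios with CIs are planned, causal inference is disclaimed, the end point is called a process measure, and larger cohorts are called for in later work on clinical outcomes. A reader might infer that the authors will report a null result as no effect, but nothing in the text says so. None of these caveats, however, mentions a shortfall in size or power for the primary end point.

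**The unit of the 35%.** A reader might infer that it is a per-prescription rate and that the required size is therefore wrong. The article supports neither that reading nor the per-patient one, and it gives no number of covered drugs per patient from which to convert. Only a request to state the unit is justified.

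**Conclusion.** The point holds as a failure to reconcile the article's own figures. The 138 per group is correct for its assumptions. On the plain reading of the enrolment count, the two windows deliver about 121 to 136 patients instead of 276. Power for 35% against 20% falls from 80% to about 45% to 50%, and the CI half-width widens from about 10 to about 15 points. These figures depend on 121 being the total, on steady accrual and on a roughly equal split. Within that reading, no choice of elapsed time or split examined lifts power above about 50%. If instead 121 is a cohort B begun about October 2025, the shortfall nearly disappears. The article does not let the reader tell which case applies, yet it still gives 138 per group and 80% power as the only statement of the study's size and power.

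**What to change.** - Report enrolment separately for cohorts A and B, with the dates of each window.
- State which rule closes accrual: the 9-month windows or the 276 target.
- If the windows close it, keep the 138-per-group calculation on record as the planning assumption. Beside it, give the actual or expected number per cohort with the resulting power, detectable difference and CI width. On the plain reading these are about 60 to 68 per cohort, 45% to 50%, about 21 points (at 64 per cohort) and about ±15 points. Then stop presenting the study as having 80% power.
- In that case, also state that the primary result will be read from the estimate and its CI, and that non-significance is not evidence of no effect.
- If the 276 target closes accrual, correct the window lengths and the results date. At the pace implied by the plain reading, 276 patients would take about 36 to 39 months.
- State whether the 35% is the proportion of patients with at least one deviation. Do not replace it with the rate observed in cohort A, because that would overwrite a planning assumption with study data.

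If the windows close accrual, the cost is a few sentences, the per-cohort counts and one recalculation, with no extra patients; the stated power may become less favourable. It is best done before the August 2026 analysis.

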#### Data Collection and Security

The following data will be collected: age, gender, admission type (standard or emergency case), average and actual length of stay, Charlson Comorbidity Index, Child-Pugh score, type of liver cirrhosis, MRPs, severity of MRPs according to the National Coordinating Council for Medication Error Reporting and Prevention [18], ward pharmacists’ recommendations for solution of MRPs, acceptance of recommendations and reasons for rejection of an intervention by physicians, and outcome of the intervention.

The authors will only have access to pseudonymized data, whereas only the ward pharmacists and ward physicians will have access to personal data.

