### Application of Dose Recommendations in Patients

#### Objective of the Clinical Study and Study Design

Finally, the feasibility and acceptability of the adopted recommendations for drug selection and dosing in liver cirrhosis will be evaluated through a prospective, nonrandomized clinical study involving patients with liver cirrhosis with the following objectives: (1) improvement of drug therapy safety by applying the consensus-validated therapy recommendations in patients with liver cirrhosis and (2) demonstration of clinical usefulness of the consensus-validated therapy recommendations for patients with liver cirrhosis. For this purpose, dose recommendations will be provided to the pharmacists responsible for the wards with hepatologic patients. If discrepancies between the prescribed medication and the adopted dose recommendations are identified in a patient meeting the inclusion criteria, pharmacists will propose a dose adjustment; substitution with an alternative active substance; or another strategy mentioned in the dose recommendations, such as TDM or enhanced monitoring for adverse reactions. The acceptance of the recommendations remains at the discretion of the prescribing physician. The clinical study will be conducted in the hepatology department of University Hospital Bonn.

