The primary objective is to assess whether implementation of the consensus-validated recommendations is associated with a lower rate of deviations from the recommendations regarding drug selection and dose adjustment. The primary comparison of deviations as defined in the Primary and Secondary End Points section between cohort A (before implementation) and cohort B (after implementation) will be performed using a chi-square test for the dichotomized end point; effect estimates will be reported as odds ratios with corresponding 95% CIs. Additionally, the raw number of deviations (counted as MRPs at the patient level) will be compared between the 2 cohorts using a nonparametric Wilcoxon rank-sum test. If substantial baseline differences between the cohorts are observed, adjusted analyses may be performed using regression models (eg, logistic regression for the binary outcome or Poisson or negative binomial regression for count data) including relevant baseline covariates to account for potential confounding. The main analysis will be conducted at the patient level. In a secondary analysis, the evaluation will be repeated at the prescription level; clustered data structures (multiple prescriptions per patient) will be accounted for using appropriate methods. As the primary objective is to compare prescribing behavior between 2 predefined cohorts within a real-world pretest-posttest design, the primary analysis will be conducted unadjusted for other covariates. To address potential bias, baseline characteristics will be described and compared between cohorts to assess potential imbalances. Furthermore, major organizational changes or parallel quality improvement initiatives related to medication safety will be documented and qualitatively considered when interpreting the results. An exploratory sensitivity analysis using logistic regression adjusting for key clinical variables (eg, age, sex, and Child-Pugh class) will be performed to assess robustness with regard to potential residual confounding. Secondary end points will be analyzed descriptively and, where appropriate, using inferential methods suited to the scale and distribution of the corresponding variables. If distributional assumptions for parametric testing are not met, appropriate nonparametric alternatives will be applied. Missing data will be handled via complete-case analysis without imputation; the extent and pattern of missingness will be described. No formal adjustment for multiple testing will be applied for secondary outcomes, and results will be interpreted accordingly. Analyses will be performed using R (version 4.4.2; R Foundation for Statistical Computing [19]) with RStudio (Posit PBC) [20]. Statistical significance will be set at a *P* value below .05.

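### Deviations are defined from prescriptions but counted as pharmacist-found MRPs, and nothing in the text ensures that cohorts A and B are scored by the same method

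*Protocol article*

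**What the plan says.** All references are to the protocol article.

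- **Definition.** Primary and Secondary End Points defines a deviation at the level of the single prescription: a covered drug prescribed in a way that does not match the recommendation. Each relevant prescription is to be checked, and the result is reduced to at least one deviation per patient, yes or no.
- **Counting.** The same section then says that the number of MRPs per patient is counted and dichotomised, and that MRPs come from the first full medication review at initial assessment. Statistical Analysis equates the two, treating the raw deviation count as a count of MRPs.
- **Data.** Data Collection and Security begins "The following data will be collected: age, gender, admission type (standard or emergency case), average and actual length of stay". The rest of that sentence adds comorbidity, Child-Pugh score, type of cirrhosis, MRPs and their severity, the ward pharmacists' proposals, acceptance, reasons for rejection and outcome of the intervention. It does not name substance, dose, interval or number of covered prescriptions.
- **Intervention.** Under Objective of the Clinical Study and Study Design, "dose recommendations will be provided to the pharmacists responsible for the wards with hepatologic patients". Cohort A covers the 9 months before implementation and cohort B the 9 months with the recommendations in use.
- **Further analysis.** "In a secondary analysis, the evaluation will be repeated at the prescription level", allowing for several prescriptions per patient.

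**The concern.** The primary comparison is interpretable only if a given deviation is equally likely to be recorded in A and in B. If the record is an MRP raised at a pharmacist's review, the intervention changes the measuring instrument. A reviewer who holds the list will notice departures from it that a reviewer without it may not. That pharmacists lack the list in cohort A is the natural reading of a before-and-after design, although the article does not say so in words.

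A difference in detection cannot be separated from a change in prescribing. The stated safeguards do not reach it. Statistical Analysis offers baseline comparisons, covariate adjustment and a log of organisational changes; the Discussion adds a stable setting, consistent physicians and consecutive periods. None of these concerns how deviations are found.

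The prescription-level analysis has a related gap. A prescription that agrees with the list raises no MRP, so a file of MRPs supplies the numerator of a prescription-level rate but not the denominator.

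**Working it through.** **1. Passages side by side**

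| Item | What it rests on |
|---|---|
| Deviation, as defined | Covered prescriptions compared with the list |
| Deviation, as counted | MRPs from the first medication review |
| Medication data listed | MRPs, proposals, acceptance, outcome |
| Who scores A, when, from which record | Not stated |
| Prescription-level rate | Deviating ÷ (deviating + concordant) covered prescriptions; concordant ones are not in the list |

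**2. The plan's own figure**

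Inputs from Sample Size Calculation and Start of Study: a sample of historical clinic data "showed an inappropriate prescribing rate of 35" percent; "It is expected that the recommendations will reduce this rate to 20" percent; "the usual .05 significance level (2 sided) and 80% power"; "138 patients per group are required, resulting in a total of 276 patients".

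Chi-square test, pooled variance, no continuity correction, p̄ = (0.35 + 0.20)/2 = 0.275:

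n = [1.960·√(2·0.275·0.725) + 0.842·√(0.35·0.65 + 0.20·0.80)]² / 0.15²
= [1.238 + 0.524]² / 0.0225 ≈ 138 per group.

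The stated 138 is reproduced, with power 80.0%. The calculation takes the recorded rates to be the true rates in both cohorts.

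**3. Illustration of unequal detection**

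Assumption, not in the article: cohort B records every patient with a deviation, and cohort A records a share s of them. The recorded rate in A is 0.35·s and in B 0.20.

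Power = Φ[(d − 1.960·SE0)/SE1], with d the recorded difference, SE0 = √(2·p̄(1 − p̄)/138) and SE1 = √{[pA(1 − pA) + pB(1 − pB)]/138}.

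For s = 0.9: pA = 0.315, d = 0.115, 1.960·SE0 = 0.103, SE1 = 0.052, giving power of about 59%.

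| s | Recorded A | Recorded B | Odds ratio (B vs A) | Power |
|---|---|---|---|---|
| 1.0 | 35.0% | 20% | 0.46 | 80% |
| 0.9 | 31.5% | 20% | 0.54 | 59% |
| 0.8 | 28.0% | 20% | 0.64 | 34% |
| 0.7 | 24.5% | 20% | 0.77 | 14% |

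At s = 0.20/0.35 ≈ 0.57 the recorded difference vanishes.

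**4. Same assumption with no true change (35% in both)**

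The chance of a significant result showing B worse is 2.5% at s = 1, 9% at s = 0.9, 24% at s = 0.8 and 48% at s = 0.7.

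**The case against.** The strongest reply is that the article already points to uniform scoring. It gives one definition for both cohorts, and cohort A cannot be scored under it without the list. It says that relevant prescriptions are checked one by one. Ethical Considerations names the clinical information system as the data source, so prescriptions could be retrieved for both periods. The 35% planning rate came from historical clinic data, so past records have been assessed before. An article also condenses, and its variable list may be a summary.

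Much of this stands, and it rules out several stronger readings that a reader might infer:

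- *That the two cohorts are in fact ascertained differently.* The article does not say so; it leaves this open.
- *That the prescription-level analysis cannot be run.* The listed data do not support it, but the source system may.
- *That the intervening pharmacist scores the outcome.* No end-point assessor is named, and the authors work on pseudonymised data, so someone else may score.
- *That further gaps in the list are defects.* It also omits items such as "deviations from recommended serum levels for drugs monitored via TDM", but these are only possible, exploratory end points, and a condensed article may leave such variables out.

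What the reply does not remove is the conflict within the text. A shared definition does not give shared detection when the count is tied to a review made with and without the list. That the source system holds prescriptions shows that uniform scoring is feasible, not that it is planned.

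**Conclusion.** The point holds in a limited form. The article defines its primary outcome from prescriptions, counts it from MRPs, and lists data that match the count and not the definition. It does not state that cohort A is scored against the same list, from the same source and by the same method as cohort B. The sample size is not in dispute.

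The size of any bias is unknown. The 59% and 34% power figures depend entirely on assumed detection of 90% and 80% in A with complete detection in B. Under that assumption the error runs toward no effect or apparent harm, so a reader should not infer that the design manufactures a benefit. Other misclassification could act differently: if MRPs unrelated to the list were counted, the direction would not be fixed.

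**What to change.** State in the protocol, before the cohorts are compared:

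- For both cohorts, extract every covered prescription (substance, dose, interval, start and stop dates) with Child-Pugh class from the clinical information system.
- Derive the primary outcome and the prescription-level outcome by applying the same locked final recommendation list to the pseudonymised data, masked to cohort where possible.
- Use pharmacist MRP records only for acceptance, reasons for rejection and outcome of the intervention.

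The cost is a larger routine-data export and some scoring work by the existing team. Recommendations that call for TDM or enhanced monitoring may not be scorable from substance, dose and interval alone, and may need a rule of their own or separate reporting.
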